## Abstract

Left hemispatial neglect (LHSN) is a frequent and disabling condition affecting patients who suffered from traumatic brain injury (TBI). LHSN is a neuropsychological syndrome characterized clinically by difficulties in attending, responding, and consciously representing the right side of space. Despite its frequency, scientific evidence on effective treatments for this condition in TBI patients is still low. According to existing literature, we hypothesize that in TBI, LHSN is caused by an imbalance in inter-hemispheric activity due to hyperactivity of the left hemisphere, as observed in LHSN after right strokes. Thus, by inhibiting this left hyperactivity, repetitive Transcranial Magnetic Stimulation (rTMS) would have a rebalancing effect, reducing LHSN symptoms in TBI patients. We plan to test this hypothesis within a single-blind, randomized SHAM controlled trial in which TBI patients will receive inhibitory i-rTMS followed by cognitive treatment for 15 days. Neurophysiological and clinical measures will be collected before, afterward, and in the follow-up. This study will give the first empirical evidence about the efficacy of a novel approach to treating LHSN in TBI patients.

**Clinical Trial Registration:**
https://www.clinicaltrials.gov/ct2/show/NCT04573413?cond=Neglect%2C+Hemispatial&cntry=IT&city=Bologna&draw=2&rank=2, identifier: NCT04573413.

## Introduction

It is estimated that every year in Europe, around 235 persons per 100,000 people are affected by Traumatic Brain Injury (TBI) (1). TBI is a major cause of mortality and morbidity in young people, and its incidence is increasing in persons aged 65 years and older (1). TBI is associated with substantial health care costs, some of which are indirect and long-term, as they are related to loss of productivity and caregiver burden (1). Moreover, TBI is a major cause of long-term disability, impacting patients' and caregivers' quality of life (2).

Left hemispatial neglect (LHSN) is a common condition associated with long-term disability in patients affected by TBI. A recent study showed that about 30% of TBI patients are affected by LHSN (3), a spatial attentive syndrome characterized by a reduced ability to attend, perceive and consciously represent the left contra-lesional space in the absence of a primary sensory deficit (3). Persons with LHSN fail to attend to any stimulus coming from the left-handed space, which can affect the ability to carry out many everyday tasks, such as walking, eating, reading, and getting dressed. Those patients are also often affected by anosognosia for hemiplegia and LHSN. This condition hinders motor and cognitive recovery, predisposes to falling, and reduces independence (3). Furthermore, LHSN in TBI is often associated with a mixture of attention, motor, memory, executive function, and processing speed deficits (1). These impairments lead to a complex cognitive and behavioral picture, which may interfere with standard cognitive treatments (i.e., visual scanning protocols or prism adaptation). Indeed, as scientific evidence for effective TBI treatment is still low, LHSN often remains an untreatable and disabling condition in this population, possibly leading to prolonged length of stay in rehabilitation and a poorer outcome (3).

Rehabilitation methods for LHSN associated symptoms were extensively investigated in persons with right cerebral stroke (4–8). Previous studies showed the efficacy of 1 Hz inhibitory repetitive Transcranial Magnetic Stimulation (i-rTMS) on visuospatial symptoms in persons with an ischemic lesion of the right hemisphere. In particular, i-rTMS was applied to the posterior parietal cortex (PPC) of the unaffected hemisphere for 2 weeks. Remarkably, the observed effects persisted 15 days after i-rTMS treatment (9–11). These results can be explained considering that spatial attention deficit in LHSN due to a right middle cerebral artery territory stroke relates to abnormal activation of the neural system that mediates attentive spatial operations in the healthy brain (12). Lesions of the right PPC (or of the inter-hemispheric connectivity) cause hyperactivity of the left hemisphere. The subsequent inter-hemispheric imbalance leads to a biased attentive allocation toward the ipsilesional space (12). Consequently, inhibition of this hyperactivity may have a rebalancing effect, reducing left spatial attention deficit in LHSN. Moreover, recent studies in stroke patients showed the possibility of improving standard cognitive treatments' efficacy (i.e., visual scanning) if i-rTMS would precede the latter on the unaffected hemisphere (13, 14).

The neural correlates of the inter-hemispheric imbalance associated with LHSN symptoms are often assessed using visual evoked potentials (VEPs). In particular, N1 is a posterior negative deflection in the VEPs, peaking around 180 ms after stimulus presentation, with greater amplitude for stimuli presented in the contralateral hemifield (15). In stroke, it has been demonstrated that LHSN is associated with a smaller amplitude and delayed latency of N1 for left presented stimuli compared to right presented stimuli (15–18). This finding suggests that, in stroke, N1 is a neurophysiological index of impairment on left stimulus processing and, thus, a sign of inter-hemispheric imbalance in LHSN (15, 18, 19). Furthermore, a recent study comparing TBI patients with LHSN against controls showed the presence of hemispheric differences in latencies and amplitudes of the N1 component of VEPs to stimuli presented on both sides (15). These data suggest that the right hemispheric stroke imbalance model could also be applied to explain LHSN symptoms in TBI. In the latter, the hemispheric imbalance could be partly due to a diffuse axonal injury affecting the white matter tracts (20).

What is still unknown is whether in LHSN due to TBI, i-rTMS on the left PPC followed by a visual scanning protocol may be an effective treatment as in right hemisphere stroke, considering that in TBI, the damage is often more widespread and multifocal (1). However, Bonnì et al. demonstrated that a 2-week protocol of i-rTMS (30 Hz Theta burst stimulation on the left PPC) applied to a person affected by LHSN due to TBI reduced the hyper-excitability of the left PPC-primary motor cortex connectivity (20). In this single case, the authors demonstrated a bilateral increase of functional connectivity in the frontal-parietal network on functional Magnetic Resonance Imaging (fMRI). The rebalancing effect induced by brain stimulation was associated with remarkable improvements in LHSN cognitive and behavioral symptoms (20).

According to this preliminary evidence, this study's central hypothesis is that LHSN symptoms in both stroke and TBI rely on similar neurophysiological correlates. Indeed, as observed for right hemisphere strokes, LHSN in TBI patients may be caused by an imbalance in inter-hemispheric activity due to the left hemisphere's hyperactivity (12, 21). Consequently, i-rTMS might have a rebalancing effect by inhibiting this hyperactivity, reducing LHSN symptoms and related disability in TBI patients.

Thus, the general aim of this randomized controlled trial is to test the efficacy of a novel therapeutic approach based on i-rTMS applied to the left PPC followed by a visual scanning treatment (VST) in comparison to the same cognitive treatment preceded by a sham stimulation on neurophysiological and clinical correlates of LHSN in a sample of TBI patients. In particular, this study's specific aims are (1) to assess the efficacy of i-rTMS applied to the left PPC + VST on the inter-hemispheric imbalance in patients affected by LHSN after TBI. In doing so, we will make use of measures of interhemispheric functional connectivity derived from N1. (2) To detail the effect of combined i-rTMS + VST on cognitive symptoms of LHSN in TBI patients as measured by specific clinical measures. (3) To assess whether the effect of the combined i-rTMS + VST treatment has the potential to promote long-lasting lessening of the behavioral manifestations of LHSN in activities of daily living.

## Methods and Analysis

### Study Design

The SMaRT TraCE trial (“Stimolazione Magnetica Ripetitiva Transcranica nel Trauma Cranio-Encefalico”; in English: repetitive transcranial magnetic stimulation in traumatic brain injury) is a single-blinded randomized controlled trial (RCT) with pre-test, post-test, and 12 weeks follow-up assessments. The design provides two parallel groups of patients with LHSN symptoms after TBI (i-rTMS + VST and SHAM + VST) with a 2:2 randomized allocation ratio in a superiority trial design. Figure 1 shows the study flowchart.

**Figure 1 F1:**
[figure not shown]
Study flow-chart. The PI or a delegate checks patient's eligibility (i.e., inclusion/exclusion criteria). Selected patients will be assessed (Pre-treatment assessment) before random allocation in the intervention or in the control group. Patients will be assessed also post-treatment and in the 12 weeks follow-up. i-rTMS, repetitive transcranial magnetic stimulation.

### Participants

Patients with LHSN due to TBI will be recruited in the Neurorehabilitation Unit of the IRCCS Istituto delle Scienze Neurologiche di Bologna. Subjects will be recruited accordingly to the following eligibility criteria:

Inclusion Criteria:

Diagnosis of TBI;Diagnosis of LHSN with specific assessment tests [asymmetry score in the Bells test > 3, (22)];Intra-hospital rehabilitation setting (ordinary hospitalization or DH);Age between 18 and 80 years;Time after injury between 3 weeks and 1 year;Level of cognitive functioning (LCF ≥ 5);Adequate language comprehension to give informed consent. Language comprehension will be considered satisfactory if equal or superior to 75% in ordinary conversation, in the presence of an aphasic disturbance or deafness. Use of eventual hearing aids is allowed. In case of doubts, a simple or language comprehension test (token test) will be administered.Presence of inter-hemispheric asymmetries in the EEG activity evidenced by qualitative evaluation;

Exclusion Criteria:

Medical instability at enrollment, defined as the acute onset of an unexplained derangement of vital parameters (i.e., temperature, blood pressure, pulse rate, respiratory rate, oxygen saturation, level of responsiveness) outside the normal range (for example, fever, acute internist conditions, etc.) and/or the onset of any new medical condition requiring unexpected additional diagnostic procedures and treatments (for example, severe pain, reduction of urinary output, etc.);Presence of epileptogenic alterations to the EEG and/or previous epileptic seizures;Presence of intracranial implants of a metallic material;Presence of devices that could be altered by i-rTMS, such as pacemakers, ventriculoperitoneal shunt, baclofen pump;Decompressive craniectomy;Drugs conditioning the state of consciousness-vigilance such as benzodiazepines;Cortical blindness and/or visual agnosia;Concomitant psychiatric disorders and/or history of substance abuse;Post-traumatic agitation;Post-traumatic complications (i.e., hydrocephalus).

The principal investigator (PI) or a delegate will check the eligibility criteria before enrollment. After verifying the eligibility criteria, the PI will provide eligible patients and their caregivers with all the information and details relative to the study in simple language.

### Intervention

Intervention is based on previous studies (4, 9, 10) and on an RCT protocol for LHSN after stroke (13). In particular, seven sessions of i-rTMS will be administered over 15 days (9). In detail, the parameters used in each session will be:

The stimulation coil will be positioned tangentially over P5 accordingly to the international EEG 10/20 system, which corresponds to the target non-lesioned left posterior parietal cortex (4);90% of the motor threshold;Frequency: 1 Hz;Each session consisted of one train of 900 pulses, which resulted in a whole stimulation period of 15 min.

The stimulation site was chosen based on previous studies. In those studies, TMS over P5/P6 (9, 23) or P3/P4 (24, 25) was shown to reduce contralesional neglect related symptoms in patients with a unilateral brain lesion.

Each i-rTMS session will last 15 min and be administered every other day (e.g., Monday-Wednesday-Friday, Monday-Wednesday-Friday, Monday).

VST is a conventional cognitive protocol based on the administration of a structured series of tasks aiming at improving spatial exploration abilities (26). It provides various visual scanning tasks to increase the patient's awareness of the LHSN clinical manifestations and teach strategies to improve spatial exploration abilities (10). VST will be administered following the i-rTMS. In particular, three different training tasks will be used:

Visuospatial training;Reading and copying training;Copying of line drawings on a dot matrix.

All training tasks include three increasing levels of difficulty, thus giving nine possible task-difficulty combinations. Each level of difficulty will be practiced until the subject will reach a level of accuracy of 75%.

The training will be carried out in 50 min sessions for 5 days a week within 15 days (10) for 11 sessions. When the i-rTMS is also carried out, the visual scanning protocol administration will immediately follow the brain stimulation.

### Control

In the control group, a SHAM placebo stimulation is implemented. SHAM stimulation parameters are the same as the intervention stimulation, but the TMS coil will be positioned at 90° on the target area. Thus, no specific cortical modulation will be implemented (SHAM stimulation). The VST protocol will be administered with the same modalities and time frame for this group, as detailed for the intervention group. All routine care is permitted for both groups during the study period.

### Outcomes

Our operational objectives and outcome measures are divided into primary and secondary endpoints to reach all aims. Our outcomes will allow us to evaluate different clinical and neurophysiological aspects of LHSN and any differential improvements induced by the rehabilitation protocol.

#### Primary Endpoint

The primary outcome is represented by a specific assessment of inter-hemispheric imbalance with connectivity indexes derived from N1 amplitude (i.e., vABI Visuospatial Attention Bias Index) (13) and latency (i.e., IHTT, Inter-Hemispheric Transmission Time) (27–29).

Visual evoked potentials (VEPs) and lateralized visual processing will be collected accordingly to a method already introduced for LHSN assessment in stroke patients (13, 17, 21).

In particular, VEPs are collected during a passive visual detection task with lateralized stimuli (13, 18) to investigate inter-hemispheric imbalance in LHSN (12, 30, 31). As reported in a previous study (13), the EEG will be recorded while patients perform the task on a computer screen. The view distance will be 50 cm from the screen. A white central fixation cross is displayed on a black background (Figure 2). Patients are instructed to fix the cross during the whole task, and whenever participants lose the fixation, feedback will be provided to recover it. A stimulus will be presented randomly on the fixation cross' either sides at a distance angle of 28° along the midline on each trial. Stimuli are 1 × 1 cm yellow squares and will be displayed for 96 ms. Before the subsequent trial, a black background with the fixation cross will be presented for 1,000 ms (Figure 2). Four blocks of 64 stimuli will be delivered, and the overall task will have an average duration of 20 min.

**Figure 2 F2:**
[figure not shown]
Visual detection task. A fixation cross is presented on a black background during the whole task. At the beginning of a trial, a stimulus is presented randomly for 96 milliseconds (ms) either on the fixation point's left or right. Before a new trial begins the fixation cross is again presented for 1,000 ms.

The EEG will be recorded from 18 Ag/AgCl-cup electrodes according to the 10/20 system referenced to the linked ear lobes. The EEG signal will be recorded from electrodes: Fz, Cz, Pz, C4, C3, P4, P3, F4, F3, Oz, O1, O2. The negative peak of the N1 will be considered to analyze amplitude in microvolt (μv) and latency in milliseconds (ms). N1 amplitude and latency will be analyzed separately for left and right-presented stimuli over P3 and P4 (13, 17). Then, indexes of inter-hemispheric imbalance will be extracted. In particular, the Visuospatial Attention Bias Index (vABI; 13) and the Interhemispheric transmission time [IHTT, (27)], which are based, respectively, on N1 amplitude and latency.

The vABI will be extracted in two steps. First, we will calculate the averaged activities of the N1 for stimuli presented on both sides from considered electrodes (i.e., mean of P3 and P4). These averaged activities will measure the two hemispheric activations after lateralized stimulus presentation. The individual differences in the activations for lateralized stimuli will be calculated according to the following formula: vABI = N1 amplitude for right stimuli - N1 amplitude for left stimuli. The vABI will be calculated as a lateralization index (32) on N1 amplitude. Such an index can measure imbalance for left and right stimuli processing as it measures the activation of the two hemispheres in response to lateralized stimuli.

Similarly, based on N1 peak latency, we will compute the IHTT (27, 28), an indicator of the EEG signal's transmission times from one hemisphere to the other. In particular, IHTT measures the difference between N1 latencies for left presented stimuli on the posterior electrodes P3 and P4 (i.e., left IHTT = N1 latency on P4 - N1 latency on P3), thus constituting a single index in milliseconds of the inter-hemispheric transmission times specifically for left presented stimuli (13).

#### Secondary Endpoints

The secondary endpoints focus on the impact of rTMS on clinical and motor indexes. In particular, we will test visual-spatial attentive functioning with a standard neuropsychological battery for LHSN assessment, the Behavioral Inattention Test [BIT; (33)]. The BIT consists of two subscales (cognitive and behavioral) with standardized scores, where lower ratings indicate a more severe visual-spatial impairment. The degree of functional independence in daily living activity (i.e., eating or reading) will be tested with the Catherine Bergegò Scale (CBS). In contrast, we will test motor ability with the Motricity Index (MI) Trunk Control Test (TCT) and the motor subscale of the Functional Independence Measure (FIM^tm^) (34, 35). Finally, attentive functioning will be tested with a specific subtest (i.e., alertness and Visual Field/Neglect) of the Test of Attention Performance (TAP), an attentive computerized battery (13, 35).

## Data Analysis

### Sample Size

The sample size was calculated using the following formula:

$$\begin{array}{l} n=\frac{2{\left(z_{\left(1-\alpha \right)}\;+z_{\left(1-\beta \right)}\right)}^{2\;}\sigma^{2}}{\delta^{2}} \end{array}$$

Where *N* is the sample size; σ2: population variance established by previous studies = 2.1; δ2: absolute error allowed for parameter estimation for vABI = 2.8; z: constant (corresponding to the value of the standardized normal random variable) that depends on the level of confidence desired for the estimation. Fixing α = 0.05 and 1 – β = 0.80, (Z_1−α_ + Z_1−β_) ^2^ = 10.5. The sample size resulting from the formula is 24. Consequently, the minimum sufficient sample to reach all aims is, assuming 10% of subjects lost to follow-up, 28 subjects (14 X group), enrolled over 1 years. In case of recruitment delays, a multicentric extension of the study will be considered to guarantee an adequate number of participants.

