If ANCOVA assumptions are verified for the primary outcome, we will analyze covariance for each neurophysiological index using a mixed-model ANCOVA with a 2X3 design. The “between” factor will be represented by the randomization group (rTMS, SHAM), whereas the “within” factor will be the assessment time (T1, T2) with T0 as a covariate. Whenever necessary, Greenhouse-Geiser correction will be applied, and corrected *p*-values will be reported in the ANCOVA. Further adjustments will be made for other possible confounding factors such as age, gender, education of the participants, and lesion location (if heterogeneity between participants in lesion locations emerges from clinical data). Besides *p*-values, effect sizes will be provided to assess the size of the treatment effect. Similar analyses will also be performed for clinical and motor outcomes after verification of ANCOVA assumptions. The BIT, the TEA, the CBS, and the motor function tests provide standard scores, separated for each test, and scores including a general performance with cut-offs that allow discriminating pathological performance. Several mixed-model ANCOVAs will be applied for every test in the 2X3 design described above. Finally, we will perform correlation analyses (both parametric and non-parametric) to evaluate the relations between the neurophysiological indices and clinical measures.

Two-tailed *t*-tests for independent samples will be employed to investigate the differences between groups. Data analysis will be performed using MatLab (The Mathworks Inc.) and SPSS (version 13). A significance level of 5% (i.e., *p*-value = 0.05), corrected for multiple comparisons when needed, will be accepted.

Additional clinical and demographic information, such as handedness of subjects, prescribed medications, and relevant medical conditions, will be recorded for each participant in specific Case Report Forms.

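### The printed multiplier 10.5 is the 90%-power value, not the stated 80%, so the power and target vABI difference behind N = 24 are undetermined; N itself can be reproduced

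*Protocol article*

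**What the plan says.** The Sample Size section of the protocol article gives the usual two-group formula for means, n = 2(z + z)²σ²/δ², with the first quantile written as z(1−α). The inputs are:

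- Error rates: "Fixing α = 0.05 and 1 – β = 0.80", followed by a squared quantile sum of 10.5.
- σ², described as "population variance established by previous studies = 2.1".
- The quantity labelled δ², described as "absolute error allowed for parameter estimation for vABI = 2.8".

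The result is: "The sample size resulting from the formula is 24". Allowing for loss, the section continues: "assuming 10% of subjects lost to follow-up, 28 subjects (14 X group". The per-group count shows that 24 is a total, that is 12 per group, although the section does not say whether the formula's n is per group or overall.

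Two other sections bear on the calculation. Study Design describes equal arms: "with a 2:2 randomized allocation ratio in a superiority trial design". Statistical Analysis fixes the sidedness of the group comparison: "Two-tailed *t*-tests for independent samples will be employed to investigate the differences between groups".

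**The concern.** The multiplier and the stated power cannot both be right. At 80% power the squared quantile sum is 7.85 two-sided or 6.18 one-sided, so no choice of sidedness turns it into 10.5. A reader who puts the printed numbers into the printed formula does not get 24.

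This is the article's only sample size justification, and it concerns the vABI, one of the two primary indices. If the inputs behind 24 are unclear, so is the difference the trial was planned to detect and the power for it. The label δ² points to a squared quantity, while its description as an absolute error points to an unsquared one.

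**Working it through.** **Inputs.** α = 0.05, power 0.80, multiplier 10.5, σ² = 2.1, δ² = 2.8 and 10% loss (Sample Size); equal arms (Study Design); two-tailed tests (Statistical Analysis).

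**Step 1: reproduce the plan's figure.** Take the stated power, two-sided 5%, and the labels as printed:

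- (1.960 + 0.842)² = 7.85
- n per group = 2 × 7.85 × 2.1 / 2.8 = 11.77, rounded up to 12, so 24 in total
- with 10% loss: 12 / 0.9 = 13.3, rounded up to 14 per group, so 28 in total

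Both stated totals are reproduced, but with 7.85 and not with the printed 10.5.

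**Step 2: identify 10.5.** Squared quantile sums at α = 0.05:

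| | 80% power | 90% power |
|---|---|---|
| one-sided | 6.18 | 8.56 |
| two-sided | 7.85 | 10.51 |

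The printed value is the two-sided, 90% entry.

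**Step 3: use 10.5 literally with the printed labels.** 2 × 10.5 × 2.1 / 2.8 = 15.75, so 16 per group and 32 in total (16 / 0.9 = 17.8, so 18 per group and 36 after loss).

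**Step 4: keep 10.5 and read 2.1 as the SD and 2.8 as the difference.** 2 × 10.5 × 2.1² / 2.8² = 2 × 10.5 × 4.41 / 7.84 = 11.81, so 12 per group and 24 in total. This also reproduces the plan, now at 90% power.

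**Step 5: other combinations.** With the printed labels, one-sided 80% gives 2 × 6.18 × 2.1 / 2.8 = 9.27, so 10 per group and 20 in total. If 2.1 is a variance and 2.8 an unsquared difference, 10.5 gives 5.63 per group (12 in total) and 7.85 gives 4.20 (10 in total). If 2.1 is an SD and 2.8 a squared difference, 10.5 gives 33.08 per group (68 in total) and 7.85 gives 24.72 (50 in total). None of these yields a total of 24.

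**Step 6: what the two surviving readings imply.**

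- Squared reading: difference √2.8 = 1.67, SD √2.1 = 1.45, d = √(2.8/2.1) = 1.15, planned power 80%.
- SD reading: difference 2.8, SD 2.1, d = 2.8/2.1 = 1.33, planned power 90%.

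**Step 7: power without the normal approximation.** Noncentral t, two-sided 5%, unadjusted comparison:

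| evaluable per group | squared reading | SD reading |
|---|---|---|
| 12 | 77% | 88% |
| 13 | 81% | 90% |
| 14 | 84% | 92% |

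With 14 randomised per group and 10% loss, 14 × 0.9 = 12.6 per group are expected to be evaluable.

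**The case against.** The strongest reply is that only an intermediate constant is wrong. The stated level read two-sided, the stated power, and the two inputs as labelled give exactly 24 and 28. On that reading power, effect size and N agree with one another, and 10.5 is a slip without consequence. That is right as far as it goes. It also disposes of the stronger reading a reader might take from Step 3, that the trial needs 32 patients and is eight short. Thirty-two is what 90% power would need under the printed labels; the article states 80%, so it does not support 32 as a requirement.

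The reply does not settle which item is the slip. Keeping 10.5 and correcting the labels reproduces 24 equally well, and the description of 2.8 as an absolute error gives that reading some support.

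Three further points for the plan stand:

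- Both readings share the same arms, the same N and the same power curve in standardised units. They differ in the raw-scale assumptions and in the power quoted, not in the design.
- The 77% figure is for 12 per group without covariates. The article prefers ANCOVA with the T0 value as covariate when its assumptions hold, which generally reduces residual variance, and 14 per group are randomised.
- z(1−α) is probably loose notation. The one-sided value produces neither 10.5 nor 24, and the stated tests are two-tailed.

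**Conclusion.** The paragraph is wrong as printed: 10.5 contradicts 80% power, or else 2.1 and 2.8 are mislabelled as squares. The document does not decide between the two. What is undetermined is therefore the planned power (80% or 90%) and the target vABI difference (1.67 or 2.8, d = 1.15 or 1.33).

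The sample size is not undermined. Both 24 and 28 are reproducible, and nothing here shows that N is too small. On the squared reading, unadjusted t-test power at 12 per group is about 3 points below the stated 80%, and it reaches 81% at 13, before any gain from baseline adjustment. It would also go too far to say that a null result becomes uninterpretable: what the data exclude will be read from the confidence interval, not from the planning difference.

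These conclusions assume a two-sided 5% test, equal arms, and 24 as a total across both groups.

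**What to change.** Keep 28 randomised and rewrite the Sample Size paragraph as follows:

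1. State whether 2.1 and 2.8 are σ and δ or their squares.
2. Print the multiplier that matches the intended power: 7.85 for 80%, 10.5 for 90%.
3. Write z(1−α/2), to agree with the two-tailed tests.
4. Say that the formula's n is per group.
5. Describe δ as the between-group difference in vABI to be detected, not as an allowed error of estimation.
6. Restate the power accordingly. If quoted from the t distribution at 12, 13 and 14 evaluable per group, it is 77%, 81% and 84% on the squared reading, or 88%, 90% and 92% on the SD reading, noted as before baseline adjustment.

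The cost is one reworded paragraph. No patients are added, and neither the allocation nor the analysis changes. The quoted power may come out slightly lower than the formula's.
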